# Effectiveness of a mobile app-based educational intervention to treat internet gaming disorder among Iranian adolescents: study protocol for a randomized controlled trial

**DOI:** 10.1186/s13063-022-06131-0

**Published:** 2022-03-21

**Keywords:** Internet gaming disorder, Transtheoretical model, Adolescents, Application, Randomized controlled trial, Cognitive-behavioral therapy, Addictive behaviors, Video games, Internet addiction disorder

## Abstract

**Background:**

The use of video games, a hobby for many teenagers in their leisure time, has brought with it a new potential for concerns. Internet gaming disorder (IGD) is a mental condition classified as a disorder due to addictive behaviors. It may include use of video games, both online and offline. Consequences of IGD may include introversion, social anxiety, mood swings, loneliness, sleep problems, behavioral problems, depression, low self-esteem, and increased violence. In order to design an app-based intervention for adolescents, a transtheoretical model (TTM) has been used. This widely used model in the field of behavioral change is also practical for health education programs. In addition, cognitive-behavioral therapy (CBT) has been used to make people more aware of their behaviors, feelings and thoughts and how to achieve behavioral change. The present study seeks to determine the effectiveness of this app-based intervention in in the treatment of IGD among adolescents.

**Method:**

In this single-blinded, randomized, controlled trial, 206 high-school adolescents aged 13 to 18 years in Qazvin city will be recruited. Eligible adolescents will be randomly assigned into intervention and control groups. Eight consecutive sessions delivered over 2 months and based on the TTM and CBT will be delivered through the `app (named HAPPYTEEN) to the intervention group. The control group will receive a sleep hygiene intervention (8 consecutive sessions for 2 months) via the app. Data collection tools include the Internet Gaming Disorder Scale, Insomnia Severity Index, Depression, Anxiety, and Stress Scales, Stages of Change Questionnaire, Decision Balance, and Self-Efficacy. The study measures will be completed at baseline, post intervention, and 1 month and 3 months after the intervention.

**Discussion:**

The results of this intervention could be used as adjunct therapy for adolescents with IGD.

**Trial registration:**

Clinical Trial Registration Center of Iran (IRCT) IRCT20181226042140N1. Registered on June 9, 2020.

**Supplementary Information:**

The online version contains supplementary material available at 10.1186/s13063-022-06131-0.

## Background

In the setting of dramatic growth of communication technologies, computer games as a social phenomenon often attract children and adolescents [1]. Some youth may experience difficulties regulating time spent playing video games, leading to addictive engagement [2, 3]. The 11th revision of the International Classification of Diseases (ICD-11) was officially adopted at the World Health Assembly [4]. Gaming disorder (GD) was included in the ICD-11 (and internet GD (IGD) was included in the 5th Edition of the Diagnostic and Statistical Manual (DSM-5®)) to define criteria for disordered patterns of gaming [4]. GD may include use of a variety of video games, whether online or offline, whereas IGD specifies the focus on gaming conducted online, often competitively in groups [5, 6]. Types and patterns of gaming may lie along a continuum from enjoyable to harmful and addictive [7].

Gaming in GD, like substance use in substance use disorders, may be motivated by desires to escape problems in life [8]. According to the American Psychiatric Association, IGD is characterized by a persistent pattern of behavior and frequent use of the internet to engage in online gaming, leading to significant disruption or discomfort over a 12-month period. Five out of 9 inclusion criteria are needed for diagnosis. These criteria include preoccupation, withdrawal, tolerance, unsuccessful attempts to limit time spent gaming, diminished interests in non-gaming activities, continued gaming despite adverse consequences, deceiving family members, therapists and others about durations of gaming, using online games to reduce negative moods, and jeopardizing relations or educational or occupational opportunities due to internet gaming [9].

In Iran, a study by the National Youth Organization shows that the number of people using the internet has grown by 70% of the population last year [10]. Zamani et al. found that of 564 seventh-graders, 17% experienced gaming problems [11], and another study reported that nearly 60% of 210 Iranian adolescents spend at least one or more hours a day playing video games [12]. More than 35% of people using the internet in Iran are youth/young adults, and the average time spent on the internet is generally 52 min per week [13].

Globally, individuals aged 16 to 21 years appear among the most vulnerable for developing gaming problems [14]. Approximately one in 21 adolescents may experience IGD [15]. However, prevalence estimates of IGD vary across jurisdictions [14]. In Spain, 0.6% of adolescents [16], and in the UK, 19.9% [17] experience gaming problems, and according to a study in Turkey, 4.5% of 16-year-olds met criteria for IGD [18]. Approximately 1.5–3% of adolescents aged 13–16 years in the Netherlands had IGD [19]. In East Asian countries, prevalence estimates may be higher [16], with males more frequently gaming and having gaming problems relative to females [4, 20]. This variability in prevalence estimates may reflect differences in assessment instruments, study populations, and the criteria for diagnosing IGD [7]. In Iran, the prevalence of gaming in children and adolescents is reported to range between 30% and 72% [21]. Another study found that 56% of young Iranians are very interested in computer games and use the internet in their spare time [21].

IGD may alter behavioral tendencies. For example, after prolonged gaming and IGD, people may experience introversion, social anxiety, mood swings, loneliness, sleep problems, behavioral problems, depression, aggression, and low self-esteem [22, 23]. However, longitudinal studies are needed to disentangle pre-existing vulnerabilities from consequences of gaming and IGD.

Successful educational interventions typically involve theoretical planning [24]. The use of behavior change models/theories may help in recognizing the factors affecting behavior change and facilitating successful intervention [25]. The transtheoretical model (TTM) is widely employed [26] and focuses on explaining how to change behavior over time [27]. This model has many applications for behavioral change, including for physical activity, smoking cessation, alcohol withdrawal and IGD among adolescents, youth, and adults [28, 29].

Few studies have used cognitive-behavioral therapy (CBT) in the treatment of IGD [30]. CBT has been used for many mental health-related illnesses including anxiety and depressive disorders and alcohol, drugs, gambling, and internet addictions [31–35]. CBT has demonstrated effectiveness in changing maladaptive behaviors [36, 37]. Due to the behavioral similarities between people who experience substance use and gambling disorders and those with IGD, some targeted domains of CBT for IGD may include stimulus control and learning of and enacting healthy coping responses when craving. Motivational understanding, self-monitoring, cognitive restructuring, and problem solving are also important considerations [30, 38, 39].

In recent years, psychological treatments have undergone considerable changes given the widespread availability of digital technologies including computers, the internet, mobile devices such as smartphones, and mobile software applications [40]. Many digital treatments are provided in the form of CBT [41]. Increased convenience, privacy, and trust in this method have increased demand for such treatments [42]. The internet is an emerging platform for mental health services worldwide [43–45]. The internet serves as a potential solution to geographic and transportation challenges and may facilitate the provision of mental health services to patients in their own homes. Internet-based CBT has shown promising results for addressing different mental problems [46–48]. Emerging evidence suggests that internet-based CBT is as effective as face-to-face CBT [48–52]. If the content of CBT-based technology that is disseminated via the internet, emails, or mobile phones is of good quality and has credible evidence-based efficacy and effectiveness, it may have widespread positive therapeutic effects and patient acceptance, similar to face-to-face CBT [53, 54]. Of note, given that gaming is often done online, appropriate precautions should be considered and used when conducting treatment for gaming problems via online platforms. Given the ubiquity of digital devices and their incorporation in many aspects of daily life for most people, such precautions will likely be beneficial in general for any intervention with IGD populations.

The study will aim to determine the effectiveness of an educational intervention based on the TTM model and CBT in the treatment of IGD in adolescents.

## Methods/design

### Objectives

The overall aim of this trial is to determine the effectiveness of an educational intervention based on the TTM model and CBT in the treatment of online gambling addiction through an app in adolescents.

More specifically the study aims are to compare in the active control and intervention groups over time (before and one and three months after):
Stages of changeSelf-efficacyThe balance of decisional choicesThe intentions to perform preventive behaviors relating to online gamingLevels of stress, anxiety and depressionIGD severityGaming durationSleep health status

### Study design

The implementation of the educational program and intervention will be online by using an app called HAPPYTEEN.

The stages of this research will briefly include educational planning, intervention implementation, and evaluation at three times (before the intervention and at 1-month and 3-month follow-ups after the intervention). The study flow diagram is provided in Fig. 1.

**Fig 1 Fig1:**
[figure not shown]
CONSORT flow diagram

In order to select the sample, a one-stage sampling method will be used. For this purpose, a list of secondary schools will be prepared. Then, out of 25 high schools, 8 will be randomly selected and screened for gaming disorder in all students who play computer games (both online and offline) using the nine-item Internet Gaming Disorder Scale - Short Form (IGDS-SF9). An online questionnaire will be provided to adolescent students through school information channels so that those who volunteer may participate in this research. Eligible adolescents (*n* = 206) will be randomly assigned into action control (*n* = 103) and intervention groups (*n* = 103). An online questionnaire will be provided to adolescent students through school information channels so that those who volunteer can participate in this research.

After approval of the ethics Committee in Research of Qazvin University of Medical Sciences (IR.QUMS.REC.1398.358), a letter will be sent to the General Department of Education of Qazvin Province to obtain all high school lists and permission to conduct the research. The first author will hold coordination meetings with school principals and explain the research clearly. After the schools’ agreement, an announcement of the study will be posted in the schools’ channels. During the COVID-19 pandemic, a specific application (the SHAD web) was developed by the ministry of education to be used for all schools for teaching, parental involvement, and other activities. Each school has this application. Screening questionnaires will be provided to the target group through these school information channels (i.e., the SHAD WEB). In addition, in all stages of the research, to ensure the participants' satisfaction, they will be provided with an explanation that all their answers and statements will be kept completely confidential and tracked by numbers. After reviewing eligibility criteria, eligible adolescents will complete baseline measures and then will be randomly divided into two groups (active control and intervention) as detailed above and below. The intervention group will receive an educational app (HAPPYTEEN) based on the TTM model and CBT. The intervention will be conducted weekly in eight sessions with an average duration of 30 min, while the active control group will receive an intervention on sleep hygiene. It should be noted that individual participants in both groups will be assigned a unique code as username (phone number or email) to enter the app. Initial feedback from an independent sample of adolescents found that the app was understandable and acceptable to adolescents. All participants’ activities (including opening each page, duration of reading each page, the number of logins) will be monitored and evaluated by an independent researcher to ensure adherence to treatment among participants. In the app user environment, participants can also communicate with the support team via email and phone message to share any questions, criticisms, and suggestions with an independent support team. Messages related to reminder training tips and reminders to answer weekly questions are possible through the app.

### Participants and procedure

#### Inclusion and exclusion criteria

Inclusion criteria for eligible adolescents to enter the trial will be as follows: voluntary participation of adolescents aged 13 to 18 years; studying in Abeyek high schools; full access to a computer or laptop, tablet or smartphone; internet access; scoring 32 or higher on the nine-item Internet Gaming Disorder Scale – Short Form (IGDS-SF9) [55]; and providing consent to participate in the study by both parents and adolescents. Adolescents with mental disabilities or severe mental health-related illness (such as schizophrenia and bipolar disorder) will be excluded. Moreover, the participants will be excluded if they do not receive more than 50% of the interventional materials. The procedure of recruitment and acquiring informed consent will be done by the second author ([name]).

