#### Randomization

Recruitment will begin on June 1, 2021. After screening the adolescents and having eligible adolescents complete the questionnaires, randomization will be conducted. This study is a two-group, parallel, single-blind randomized controlled trial with a sample size of 206 adolescents. From a total of 25 schools, 8 schools will be randomly selected by simple randomization methodology. A list of schools will be provided by referring to the Department of Education. All high schools will be considered eligible to have the opportunity to reach students of all different socioeconomic levels. After checking the eligibility of the adolescents, of the 206 participants’ schools, 103 adolescents will be randomly assigned to the intervention group, and the other 103 adolescents randomly assigned to the active control group by simple randomization methodology. The simple randomization will be done to assign participants for study groups by an independent statistician with a 1:1 allocation.

From each school, the students selected will receive a special code through SPSS software, and after analyzing the data, they will be selected randomly through these codes.

Blindness will not be performed in study participants due to the different natures of the approaches in the active control and intervention groups, with one group receiving educational training on IGD and the other receiving educational information on sleep hygiene. Study administration and the statistician will be blinded to group allocation.

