The next TTM domain considered is decisional balance. Decision-making is the process by which an individual considers the outcome of mental agreements (positive mental images, values, and beliefs) and oppositions to engage or not in behaviors. This domain is similar to that of perceived benefits and barriers in the health belief model [56]. The balance between perceived agreements and disagreements often fluctuates throughout stages of change.

Self-efficacy is the third domain considered for the intervention group. This domain, which comes from Bandura's theory of social learning, is a person’s self-efficacy and has a linear and positive relationship with the domain of stages of change. If a person goes to higher stage of change, his/her self-efficacy also increases [57].

The present study will focus on three domains of the TTM model (i.e., stages of change, self-efficacy and decision balance) in order to investigate the role of the TTM model in the treatment of IGD. One of the reasons for selecting these three domains is their success in statistically predicting individuals’ addictive gaming behaviors, which has been examined and demonstrated in a previous study [58].

Beside the TTM model, CBT will be used for our intervention. CBT is a form of psychotherapy that helps people understand thoughts and feelings that influence their behaviors. During treatment, a person learns how destructive or disturbing thoughts may have negative effects on their behaviors [59], and they may learn coping skills to manage their thoughts and feelings in a more healthy fashion [30].

After installing the app, each individual enters into the study with a use code that can be a mobile phone number or email that is recorded in the initial screening of each person in the study. Thereafter, a confirmation code is received via SMS.

The main page of the app consists of 4 sections: 1. content of training sessions, 2. exercises and weekly assignments, 3. questionnaires, and 4. a progress chart. The trainings are designed for 8 consecutive weeks (one session per week), and the approximate duration of each session is 30 min. Training includes written texts, videos, and audio files (relaxation music, relaxation exercise, and audio stories). Table 1 provides an overview of the content of each session in the intervention group (Screenshots of the app is provided in Additional file 1).

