### Sample size/power calculation

The sample size for the study was estimated based on a pilot study of 12 adolescents with IGD. The results of the pilot study showed that adolescents reported lower scores on the IGDS-SF9 at post-treatment follow-up (pre-treatment *M* = 34.59, *SD* = 16.91; post-treatment *M* = 25.37, *SD* = 17.94). However, 2 adolescents did not complete the post-treatment assessments. It is hypothesized that the app-based intervention will have at least a moderate mean effect size of 0.50 (Cohen’s *d*) compared to the control group. Using G*Power [61], sample size was calculated assuming a power of 90% for a two-group comparison analysis with three measures over time, the significance level of 0.05 and loss to follow-up of approximately 20%. The final sample size was set at 103 participants for each group.

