##### Primary outcome measure

The primary outcome measure will be the IGDS-SF9. The IGDS-SF9 assesses the severity of IGD in adolescents [6, 62]. These activities include any game, whether online or offline performed through consoles, computers, laptops, tablets, and smartphones. The IGDS-SF9 has 9 items correspond to the nine IGD criteria defined by the DSM-5. All items are rated a five-point Likert type scale from 1 (never) to 5 (always). The total score is obtained by summing all 9 responses and range from 9 to 45 with higher scores indicating a higher risk of developing IGD. The Persian version of the *IGDS-SF9* was found to be highly valid and reliably among Iranian adolescents [62].

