##### Assessment of adherence

Participants’ adherence to the interventions will be assessed by calculation the length of time using the app and number of log-ins using an online database. Moreover, the online database will be used to assess each participant’s viewing of each page and time spent on it.

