### Statistical analysis

A blinded biostatistician will analyze the data using SPSS version 25 and MLwiN version 2.27 software. An intention-to-treat analysis will be used to compare the intervention effects between the active control and intervention groups. The Kolmogorov–Smirnov test will be used to assess normality distribution of study variables. Multilevel linear models (MLMs) using a random-effects model will be conducted to compare primary and secondary outcome measures across the two groups over baseline and at 1 month and 3 months after the intervention. Within-group intraclass correlations will be calculated, and a two-level mixed model will be used with adolescents nested in time.

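### Excluding participants who receive half or less of the material is a post-randomisation rule that, as written, conflicts with the intention-to-treat analysis and opens the primary comparison to selection bias of unknown size and direction

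*Protocol article*

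**What the plan says.** The Inclusion and exclusion criteria section ends its exclusions with this rule: "Moreover, the participants will be excluded if they do not receive more than 50% of the interventional materials". It does not say what the participant is excluded from.

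The Statistical analysis section names one analysis population: "An intention-to-treat analysis will be used to compare the intervention effects between the active control and intervention groups".

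On timing, the Study design section says that "eligible adolescents will complete baseline measures and then will be randomly divided into two groups". The Intervention condition section then describes eight weekly sessions, each unlocked seven days after the one before. Under Assessment of adherence, "adherence to the interventions will be assessed by calculation the length of time using the app and number of log-ins", together with page views.

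On content, the Randomization section explains that participants are not blinded, "with one group receiving educational training on IGD and the other receiving educational information on sleep hygiene". On the endpoint: "The primary outcome measure will be the IGDS-SF9".

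No section of the article limits the 50% rule to a per-protocol or sensitivity set, or says that adolescents who fall under it are still followed and analysed.

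**The concern.** An eligibility criterion has to be decidable before randomisation. This one is not: at allocation nobody has received any session. In practice it removes randomised adolescents according to what happens during the programme, which is a per-protocol restriction. A team that applies the sentence literally and a team that applies the intention-to-treat sentence literally would analyse different people for the primary outcome.

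Randomisation protects the comparison only while everyone stays in the arm they were given. Here the arms receive different material (gaming training or sleep education) and participants know which. The reasons for stopping early may therefore differ between arms and may be related to gaming severity, which is what the primary outcome measures. If so, the adolescents left in the two arms are no longer comparable, and a difference could appear, or be hidden, without any effect of the app.

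**Working it through.** **Step 1: order of events.**
1. Screening and baseline questionnaires (Study design).
2. Randomisation (Study design; Randomization).
3. Eight sessions released weekly, with use logged (Intervention condition; Assessment of adherence).
4. Follow-up at 1 and 3 months after the intervention.

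Receipt of more than 50% can be judged only during or after item 3, so the rule can act only on people already randomised. This step needs no assumption, and the conflict with intention-to-treat follows from it.

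**Step 2: inputs for an illustration.** The plan gives no figure for expected exclusions or for their prognosis. From the document come 103 per arm and the planned effect, "at least a moderate mean effect size of 0.50". (The 103 is consistent with a two-sample t-test: 86 per group for d = 0.50, 90% power and two-sided 5%, and 86 × 1.2 = 103.2. The point does not depend on this.) Assumed: the excluded shares q_i (intervention) and q_c (control), and the correlation r between engagement and improvement. The true effect is set to zero.

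**Step 3: first route.** Let engagement be standard normal and remove its lowest share q. Mean engagement of those retained is λ(q) = φ(z_q)/(1 − q):
- λ(0.10) = 0.1755/0.9 = 0.195
- λ(0.20) = 0.2800/0.8 = 0.350
- λ(0.30) = 0.3477/0.7 = 0.497
- λ(0.40) = 0.3863/0.6 = 0.644

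Bias in SD = r × [λ(q_i) − λ(q_c)]. For 30% against 10% and r = 0.3: 0.3 × (0.497 − 0.195) = 0.091. The type I error uses the numbers left, 103(1 − q) per arm, and the slightly reduced variance after truncation.

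| Excluded, intervention / control | r | Bias, closed form (simulated) | Two-sided type I error, closed form (simulated) |
|---|---|---|---|
| 20% / 10% | 0.3 | 0.046 (0.045) | 6.1% (6.0%) |
| 30% / 10% | 0.2 | 0.060 (0.058) | 6.7% (6.6%) |
| 30% / 10% | 0.3 | 0.091 (0.088) | 9.0% (8.6%) |
| 30% / 10% | 0.4 | 0.121 (0.120) | 12.5% (11.9%) |
| 40% / 10% | 0.3 | 0.135 (0.134) | 13.3% (13.0%) |
| 20% / 20% | 0.3 | 0 | 5.0% |
| 10% / 30% | 0.3 | −0.091 | 9.0% |

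A positive bias favours the app. The first five rows span about 0.05 to 0.13 SD and 6% to 13%. They do not include the extreme pairings of the same inputs: 20%/10% with r = 0.2 gives 0.2 × 0.155 = 0.031 SD (5.5%), and 40%/10% with r = 0.4 gives 0.4 × 0.449 = 0.180 SD (about 21%).

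**Step 4: second route.** If the excluded do g SD worse than the retained, removing a share q shifts an arm's mean by q × g, so bias = (q_i − q_c) × g when g is the same in both arms. With g from 0.3 to 0.8 (assumed):
- 20% against 10%: 0.03 to 0.08 SD, type I error 5.5% to 8.3%
- 30% against 10%: 0.06 to 0.16 SD, type I error 6.7% to 17.5%
- 20% against 20%: 0 SD, 5.0%

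Against the planned 0.50 SD, this route's range is 0.03/0.50 = 6% to 0.16/0.50 = 32%.

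Equal exclusion rates protect the comparison only if those excluded also have the same prognosis. With different g in each arm the bias is q_i g_i − q_c g_c; for example 0.20 × 0.8 − 0.20 × 0.3 = 0.10 SD at equal rates.

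**The case against.** **The word excluded is not tied to the analysis.** It could mean leaving the programme, or a per-protocol set, and the only sentence that names the analysis population says intention-to-treat. Analysis sets are often defined in a statistical analysis plan, which is not shown. This stands in part: a compatible reading exists, and one cannot say that the sponsor has abandoned intention-to-treat. But the rule is stated among the exclusion criteria with no such limit, so the defect is a stated rule that clashes with another, not a missing detail.

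**Receiving is not the same as engaging.** Content unlocks by the calendar, and the adherence measures are not linked to the 50% rule. That stands: it is an inference that the adolescents removed are those who use the app little. It does not change the timing, since receipt comes after randomisation either way.

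**The direction is open.** A reader might infer that adolescents unwilling to cut down gaming would drop out of the gaming programme and that the rule therefore flatters the app. The document does not establish this. It says the app is personalised by stage of change, sends those in the two earliest stages to session 1, and ties later-stage content to weeks six and seven. If more motivated adolescents start later, which the text does not say, they might receive less material, and the bias would run against the app.

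**The arms match in format.** Both have eight sessions over two months in the same app, with text, video and audio, so exclusion rates may be similar. That is possible, and with equal prognosis there would then be no bias.

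**Missing data remain.** The questionnaires sit inside the app, and about 20% loss to follow-up is already allowed for. Some adolescents caught by the rule would have no outcome data anyway. The bias added by the rule is therefore probably smaller than in a comparison with complete data, and deleting the sentence will not by itself give complete follow-up.

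**Conclusion.** The conflict is real and rests on the text alone: a rule that can act only after randomisation is listed as an exclusion criterion, and the analysis is declared to be intention-to-treat. It must be resolved because it decides who enters the primary comparison.

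The consequence is exposure to selection bias, not a demonstrated bias. The figures of about 0.05 to 0.13 SD and 6% to 13% type I error are illustrations. They depend on assumed exclusion rates and an assumed correlation that appear nowhere in the document, and on more exclusion in the intervention arm. The bias can be zero, larger, or of opposite sign under other equally unsupported inputs. The stronger conclusion, that the rule biases the trial in favour of the app, is not supported.

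**What to change.** 1. Remove the 50% sentence from the exclusion criteria.
2. State that the 1- and 3-month questionnaires will be sought from every randomised adolescent, whatever their use of the app.
3. State that the primary model includes all randomised adolescents in the arm to which they were allocated.
4. Keep the threshold of more than 50% only to define a secondary per-protocol set, labelled as such and applied identically in both arms.

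The cost is a change of wording in the protocol and analysis plan, plus the effort of pursuing questionnaires from adolescents who have stopped using the app. The planned 103 per group need not change on account of this point.

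The estimated effect may be somewhat smaller, because those who received little material now count. As an illustration, suppose the effect is 0.50 SD in those who receive the material and zero in a share q of the intervention arm who do not. The effect over all randomised is then 0.50 × (1 − q): 0.45 at q = 10% and 0.40 at q = 20%. With all 103 per group analysed, power = Φ(d√(103/2) − 1.96), which is about 90% and 82%. Both the shares and the zero effect are assumptions.
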